### 5.2. Secondary Endpoints

Length of hospital stay.

Length of index hospital stay will be measured in calendar days from admission for the index surgical hospitalization to discharge. In accordance with the approved protocol, a prespecified secondary analysis will compare length of stay between randomized groups among “cases without complications.” The protocol does not further operationalize this phrase. The statistical analysis plan (SAP) will prospectively define this subgroup, before database lock and without examination of treatment effects, as participants who remain free of a Clavien–Dindo postoperative complication during the index hospitalization before discharge. This definition is intentionally distinct from the primary complication outcome, which is assessed through postoperative day 30. Because subgroup membership is determined after randomization and may itself be affected by RESET, restriction to this subgroup does not preserve the randomized comparison and may introduce selection bias; a causal interpretation of the between-group difference is therefore not available. The analysis will be reported as a conditional, descriptive/associational comparison.

The overall effect of randomized assignment on index-hospital length of stay will be assessed separately in a complementary intention-to-treat analysis including all randomized participants, irrespective of postoperative complications. If the distribution of length of stay does not meet the assumptions of conventional linear models, regression methods appropriate to its distribution will be used.

2.Overall health status of patients.

Overall health status will be evaluated as a multidomain secondary outcome using protocol-defined measures: patient-reported and clinical scales, including SF-36 and HADS; laboratory parameters and allostatic load measures; physical-function tests, including the six-minute walk test, handgrip strength, FEV1, and sit-to-stand performance; and anthropometric and nutritional measures, including BMI, WHR, and bioelectrical impedance analysis. Each component will be analyzed separately using its validated score or original measurement unit. Changes from baseline (21 ± 7 days before surgery) to hospital admission and to follow-up at day 30 ± 5 after surgery will be compared between study arms, where the applicable assessment is completed. HADS anxiety and depression subscale scores will additionally be reported separately using their validated scoring conventions, while the protocol-defined HADS-T ≥ 15 threshold remains the clinical referral criterion.

3.Patient satisfaction.

Patient satisfaction will be assessed using a dedicated questionnaire. Patient satisfaction affects adherence to medical recommendations and overall perceptions of healthcare system effectiveness.

4.Compliance.

Compliance will be monitored via wristbands, the mobile application, and follow-up visits. Adherence to prehabilitation recommendations is clinically relevant to the evaluation of the RESET pathway and will therefore be documented prospectively as a secondary and implementation outcome.

5.Effectiveness of Stochastic Organizational Support Network Planning.

The number of interventions within the SOSNP and participants’ waiting times for the aforementioned specialist consultations will be compared to the average patient waiting time in the standard NHF system.

6.Costs associated with RESET.

Treatment costs will be measured on the basis of the analysis of costs associated with hospitalization, prehabilitation, rehabilitation, postoperative follow-up visits, and any PH/RH, as well as financial effectiveness indicators. A comparative analysis of treatment costs between patients in the RESET intervention group and those in the control group will also be conducted.

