The primary objective is to determine whether assignment to the integrated RESET pathway, compared with standard perioperative care, reduces the occurrence of: (1) prolonged index hospitalization, (2) unplanned hospital readmission within 30 days after discharge, and (3) postoperative complications. Each outcome will be evaluated separately within each of the two predefined clinical populations, yielding six primary hypothesis tests rather than a co-primary framework requiring simultaneous significance of all three outcomes. Confirmatory conclusions will be made only for the specific outcome-population hypotheses that satisfy the multiplicity-controlled decision rule specified in the Statistical Methods section of this paper. The secondary objectives are to:Evaluate the length of index hospital stay;Evaluate changes in multidomain overall health status, including patient-reported, laboratory, nutritional, anthropometric, psychological, and physical-function measures;Assess patient satisfaction and adherence to the individualized prehabilitation pathway;Evaluate the effectiveness of Stochastic Organizational Support Network Planning in facilitating specialist consultations;Compare direct healthcare costs associated with RESET and standard care;Assess implementation, continuity of care, and the potential scalability of the integrated pathway.

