### 4.2. Exclusion Criteria

-Cancer diagnosis.

Up to 12,800 potentially eligible patients will be approached and screened. At the stage of offering participation, approximately 25–35% of eligible patients are expected to decline; a 30% non-participation rate is assumed for planning purposes. Individuals who decline will not undergo study procedures, although routinely available clinical outcomes may be used in prespecified exploratory comparisons where permitted. Approximately 8960 participants are therefore expected to provide consent and be randomized. Randomized participants are allocated to the RESET intervention (90%) or standard-care control arm (10%). Both randomized arms undergo the protocol-defined assessment schedule; only the intervention arm receives the coordinated RESET pathway.

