
Additionally, the RESET tool includes the following:Stochastic Organizational Support Network Planning: This is a model that reduces patient waiting times for specialist visits and improves resource allocation by optimizing niche specialist service availability;The Enhanced Recovery Protocol: This protocol focuses on maintaining nutrition, promoting early mobilization, and effective pain management [35,36,37];The Transitional Care Program: This program provides continuous monitoring and support after discharge to prevent rehospitalization, ensure follow-up care, and manage potential risks before complications arise [38].

Moreover, the SAFER Patient Flow Bundle [39] will be implemented to shorten patient stays and enhance the efficiency and safety of patient flow. The SAFER bundle is a practical strategy designed to minimize delays for adult patients in inpatient units. This practical tool combines five core best practices. Applying all five elements simultaneously is crucial for maximizing the overall benefits. When applied consistently, the SAFER bundle shortens patient stays and enhances the efficiency and safety of patient flow. The SAFER Patient Flow Bundle consists of the following:S (Senior Review): Every patient should receive a review by a senior clinician before midday. This clinician must have the authority to make care management and discharge decisions.A (All Patients): Each patient should be given an expected discharge date and clinical criteria for discharge, assuming an optimal recovery path with no unnecessary delays.F (Flow): Patient flow should begin promptly, transferring patients from assessment units to inpatient wards as early as possible.E (Early Discharge): The goal is for 33% of patients to be discharged from inpatient wards before noon.R (Review): A structured, multidisciplinary team assessment is required for patients with prolonged stays (over 7 days), with a focus on a “home first” approach.

Each of these elements is integral to achieving smoother patient transitions and optimizing hospital resources.

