Ideally, preparation for treatment should begin during the patient’s first outpatient consultation. However, possession of a hospital referral does not automatically grant access to such a consultation. A separate referral to the appropriate specialty clinic is required. During the outpatient visit, the hospital physician—operating within a standardized time window for each patient—obtains a comprehensive medical history, including comorbidities, reviews diagnostic tests and imaging, orders additional examinations as needed, and prepares a hospital admission qualification sheet or other relevant documentation. The physician also screens for addictions, evaluates nutritional status, and collaborates with the patient to establish a preliminary treatment plan. Smoking cessation is encouraged, and intensive nutritional support may be prescribed. In cases of malnutrition or high nutritional risk, recommendations may include intensive nutritional therapy or, in severe cases, referral for percutaneous endoscopic gastrostomy placement. All of these activities must be completed within the allotted 15–20 min appointment duration.

In principle, patients awaiting surgery may pursue necessary specialist consultations; however, this is often difficult due to organizational constraints within the healthcare system and extended waiting times for certain outpatient services. Although the standard approach aims to identify perioperative risks and support appropriate preparation by surgical and anesthesia teams, its effective implementation is frequently challenging.

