7. Physical functioning will be assessed via the Zubrod–ECOG–WHO scale (Eastern Cooperative Oncology Group), which is commonly used to evaluate the general condition and quality of life of cancer patients and in geriatrics, psychiatry, and chronic diseases.

8. The Charlson Comorbidity Index (CCI) will be used to estimate the 10-year survival probability in patients with multiple comorbidities.

9. Venous thromboembolism risk will be evaluated using the Caprini scale.

10. An assessment using the G8 scale for geriatric screening will be performed.

11. For older adults, a health status assessment will be conducted using the Vulnerable Elders Survey (VES).

12. The participant’s need for specialist consultations will be assessed (coordinated under SOSNP).

13. Blood will be collected for laboratory testing (CBC, electrolytes, albumin, cholesterol, total protein, triglycerides, TSH, FT3, FT4, iron, vitamin D3, AST, ALT, and GGTP) and biobanking. At the 4th Military Clinical Hospital, the protocol-defined allostatic load panel will additionally be assessed.

14. A nutritional assessment, including anthropometric measurements (BMI, WHR), a nutritional status evaluation using bioelectrical impedance analysis (BIA), and a clinical dietitian interview will be conducted.

15. A psychological evaluation will be conducted (HADS, MMSE).

16. Physiotherapy assessment: Grip strength (dynamometer), a six-minute walk test (6MWT), a FEV-1 test, and a sit-to-stand test (using a wristband) will be conducted.

17. A participant activity assessment will be conducted using a smart wristband. A mobile app will be installed on the participant’s smartphone that will store and cycle data from the wristband, such as step count, sleep duration, and heart rate. Training will be provided on wristband usage, measurement techniques, app functionality, and technical support.

18. Clinical pharmacist assessment: A medication review will be conducted.

19. Addiction-related re-education will be conducted (if applicable).

The collected data will serve as a baseline for evaluating study endpoints (initial assessments).**Visit 2: Summary Prehabilitation Visit (Hospital Admission Day For Surgery)**

1. Health Status Update: A targeted interview will be conducted to assess any changes in the participant’s general health status since the first visit. A visit form will be completed, and scales will be reassessed for comparison with Visit 1 results.

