2. Specialist Consultation Needs: An assessment will be conducted to identify any specialist consultation needs of the participant.

3. Treatment Plan Discussion: The treatment plan, including the surgery date and discharge schedule, will be discussed with the patient and caregiver (if applicable).

4. Nutritional Assessment: A dietary evaluation, anthropometric measurements (BMI, WHR), and a nutritional status assessment will be conducted using bioelectrical impedance analysis (BIA) and a clinical dietitian interview.

5. Psychological Assessment: A psychological assessment will be performed using the HADS.

6. Physical Therapy Assessment: Physical functionality will be evaluated through grip strength testing (with a dynamometer), the 6MWT, an FEV-1 test, and a sit-to-stand test with a smart wristband.

7. Activity Level Evaluation: The participant’s activity level will be assessed through data analysis using the data from the dedicated mobile application.

8. Clinical Pharmacist Evaluation: An assessment by a clinical pharmacist will be conducted.

9. Substance Cessation Assessment: An evaluation related to substance cessation will be conducted.

10. Medical Laboratory Diagnostics: Blood tests will include a CBC and measurement of electrolytes, albumin, cholesterol, total protein, triglycerides, TSH, FT3, FT4, iron, vitamin D3, AST, ALT, and GGTP. At the 4th Military Clinical Hospital, the protocol-defined allostatic load panel will additionally be assessed.

11. Participant Satisfaction Survey: A satisfaction survey will be conducted to assess the participant’s experience with the prehabilitation program.

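### The effectiveness of specialist-access planning (SOSNP) is judged against an external NHF average wait, although a randomized standard-care arm is available

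*Protocol article*

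**What the plan says.** The Introduction lists as a secondary objective: "Evaluate the effectiveness of Stochastic Organizational Support Network Planning in facilitating specialist consultations". Section 4.3 describes SOSNP as part of the RESET tool: "This is a model that reduces patient waiting times for specialist visits and improves resource allocation".

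Section 5.2, item 5, gives the measure. It names the number of interventions within SOSNP, and then says that participants' waits for the specialist consultations already mentioned "will be compared to the average patient waiting time in the standard NHF system". No control-arm comparison of waits appears there or elsewhere in the article.

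The design does contain a concurrent comparator. Section 4.2 says: "Both randomized arms undergo the protocol-defined assessment schedule; only the intervention arm receives the coordinated RESET pathway". In section 4.5.1, Visit 1 (item 12) covers the participant's "need for specialist consultations will be assessed (coordinated under SOSNP"), and Visit 2 (item 2), on admission day, repeats the check: "An assessment will be conducted to identify any specialist consultation needs of the participant". Under standard care (section 4.3), "patients awaiting surgery may pursue necessary specialist consultations", although the article adds that this is often hard and that some outpatient waits are long.

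**The concern.** The objective is worded as effectiveness, which asks what waits would have been without SOSNP. In this trial the randomized control arm supplies that answer: same hospitals, same calendar period, same eligibility, and consultations sought through the ordinary system. The NHF average describes a different set of people, not necessarily awaiting major surgery, and its urgency mix need not match. A difference between RESET participants and that average can come from who they are and how urgently they are referred, as well as from SOSNP.

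The sentence also has a units problem. A number of interventions has no counterpart in an average waiting time, so the first half of the measure has no comparator.

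What is at stake is one stated secondary objective. Section 5.4 says that RESET is meant to inform system-level implementation and possibly reimbursement, and that false-positive conclusions would be costly. A claim that SOSNP shortens waits would feed directly into that use.

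**Working it through.** **1. Is the comparator a fixed choice?** Yes. Item 5 names it. Three other places in the article set it in context:

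- Section 5.2, item 6 (costs), the next item in the same list, does compare RESET with the control group.
- Section 5.3 defines two tracks: randomized comparisons, and an exploratory comparison with non-participants for prolonged hospitalization, readmission, length of stay and complications. A comparison with an NHF average belongs to neither.
- Section 5.3 requires balance and overlap checks before non-participant comparisons are interpreted. Item 5 carries no such safeguard.

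The article gives no NHF mean, spread or power figure for this outcome, so there is no stated figure to reproduce and the bias from the comparator cannot be sized.

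**2. Would a limited observation period add bias?** Only under a counting rule that the article does not state. Suppose that only consultations completed within W days enter the average, that waits are exponential with true mean m, and that SOSNP has no effect. Then

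observed mean = m − W·e^(−W/m) / (1 − e^(−W/m)), and share completed = 1 − e^(−W/m).

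For m = 60 and W = 21 (the preoperative period in section 4.4 is 21 ± 7 days): e^(−0.35) = 0.705, so the observed mean is 60 − 21 × 0.705/0.295 ≈ 9.9 days, with 30% completed.

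| Assumed true mean m (days) | W = 14 | W = 21 | W = 28 | Share completed, W = 21 |
|---|---|---|---|---|
| 30 | 6.5 | 9.3 | 11.9 | 50% |
| 60 | 6.7 | 9.9 | 12.9 | 30% |
| 90 | 6.8 | 10.1 | 13.3 | 21% |
| 180 | 6.9 | 10.3 | 13.6 | 11% |

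If consultations also counted up to the follow-up at day 30 after surgery, W would be about 21 + 30 = 51 days. The same formula then gives 18.6, 21.9 and 23.7 days for m = 30, 60 and 120. The effect is smaller, but it remains if uncompleted consultations are dropped. If they are followed up or censored, this truncation does not occur.

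**3. Is a randomized comparison feasible?** Section 5.4 plans 570 + 320 = 890 controls and 5170 + 2900 = 8070 RESET participants. The share needing a consultation, f, is not given, so a range is assumed. As a rough guide, for a difference in means at two-sided α = 0.01 and 95% power without multiplicity adjustment:

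detectable difference in SD = (2.576 + 1.645) × √(1/(f·n_control) + 1/(f·n_RESET)).

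For both populations and f = 0.25: 4.221 × √(1/222.5 + 1/2017.5) = 4.221 × 0.0706 ≈ 0.30 SD.

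| Assumed f | Both populations | Oncology | Non-oncology |
|---|---|---|---|
| 10% | 0.47 | 0.59 | 0.79 |
| 25% | 0.30 | 0.37 | 0.50 |
| 50% | 0.21 | 0.26 | 0.35 |

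The comparison is feasible unless few participants need a consultation. It is weakest in the non-oncology population.

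**The case against.** The strongest reply is that this is an organizational outcome outside the six-test confirmatory family, with no p value attached. Benchmarking an access tool against the system it is meant to improve is relevant context. The Discussion also warns that process measures, including specialist access, cannot show which component causes a treatment effect. This limits the consequence but does not repair the comparator. The warning concerns attribution of clinical benefit, whereas item 5 offers the waiting-time contrast itself as evidence of effectiveness.

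A second reply is that the NHF average is undefined, and that the reference to the consultations already mentioned leaves room for specialty-matched figures. That stands, and a mismatch of specialties should not be asserted. Matching on specialty would still leave different patients and urgencies.

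A reader might also infer that the preoperative window of about 21 days makes RESET waits short by construction, and so guarantees a large false benefit (1 − 9.9/60 ≈ 84% in the example). The article does not support that. It neither caps waits at surgery nor excludes later consultations. Needs are reassessed on admission day, contact continues to day 30 ± 5 after surgery, and the handling of open consultations may be left to the analysis plan.

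Finally, nothing shows that control participants' outside consultations are dated, so the randomized comparison has a real data cost. That also stands.

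**Conclusion.** The point holds for the comparator. Item 5 fixes a non-randomized external average for an objective worded as effectiveness, while a randomized standard-care arm on the same assessment schedule goes unused for this outcome. As written, the result cannot separate SOSNP from differences in patients and urgency. The pairing of a count with a waiting time is a further flaw in the same sentence.

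No size can be put on the comparator bias, because the NHF average is not given. The truncation figures illustrate a conditional risk. They rest on exponential waits, assumed means and an unstated counting rule, and they do not show that the analysis will be biased in this way. The matter is confined to one secondary objective. The six primary tests are unaffected, and the change is worth making because it is cheap.

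**What to change.** Replace the comparison in section 5.2, item 5, along these lines: within each population, time from identified consultation need to completed consultation will be compared between the randomized arms as a time-to-event outcome, with consultations still open at the end of follow-up censored; the proportion of needed consultations completed before surgery will be reported by arm; the NHF average and the number of SOSNP interventions will be descriptive context only.

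The cost is one analysis sentence and, where not already captured, a need date and a consultation date in both arms. In controls these will come partly from participant report, and a field at Visit 2 alone would miss consultations held after admission, so the day-30 contact should ask as well. Recruitment began on 16 February 2026, so dates for controls already enrolled may be hard to recover.

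Two limits should be stated with the result. Precision depends on how many of the roughly 890 controls need a consultation. Visit 1 lists randomization before the need assessment, so need should be recorded by the same criteria in both arms and its frequency shown by arm; otherwise the groups with an identified need may not be comparable.

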### 5.3. Study Conditions and Analytic Strategy

The study includes two clinical populations, oncology and non-oncology, each randomized to intervention or control. Prespecified exploratory analyses may additionally include a naturally formed non-participant comparison group for routinely available clinical outcomes. Repeated outcomes measured at two or more protocol-defined time points will be analyzed using models that account for within-participant change, between-group effects, and relevant covariates. Outcomes measured once will be analyzed using endpoint-appropriate regression models.

The analysis has two complementary tracks. The primary randomized track comprises randomized comparisons of the RESET and standard-care arms. A secondary exploratory track may compare routinely available outcomes—prolonged hospitalization, readmission, length of stay, and postoperative complications—with the non-participant group. Patient-reported and participant-specific outcomes, including multidomain health status, satisfaction, and adherence, will be analyzed only among consenting randomized participants.

Exploratory comparisons with eligible non-participants will be kept separate from the randomized analyses. Because RESET includes clinically heterogeneous operations and specialty-specific risk profiles, a single propensity-score model would not be appropriate across all surgical populations. Where propensity-score methods are used, the model will be defined prospectively within clinically coherent groups before outcomes are compared. Adjustment will be limited to characteristics recorded before the decision to participate and available in a comparable form for both participants and non-participants. The covariate set will be selected from routinely available demographic, center, calendar-period, and procedural characteristics, with additional specialty- or procedure-specific baseline factors included when clinically relevant and consistently available. Variables arising after study participation will not be used. Covariate balance and overlap between groups will be checked before adjusted comparisons are interpreted. These analyses will remain exploratory and will not influence the primary randomized treatment-effect analyses. For transparency, the prespecified core covariate set for any propensity-score analysis will comprise age, sex, study site, calendar year, ASA physical status class, Charlson Comorbidity Index, and broad surgical-procedure category. Propensity-score analyses will be undertaken only within clinically coherent groups in which these core variables are recorded before the decision to participate and are available in a comparable form for participants and eligible non-participants. Any additional specialty- or procedure-specific baseline covariate must be clinically justified and defined before outcome comparison and must be consistently available in both groups.

Analyses of accumulated data may be conducted annually to support implementation monitoring and prespecified interim publications. Final analyses will be performed after completion of follow-up. Study year and site may be included as covariates to evaluate temporal and center-related variation; these analyses will not replace the prespecified randomized comparison.

